### Outcome measures

Evaluations will be performed prior to therapy (pre-intervention [T0]), after 24 sessions of PBM + physical therapy (post-intervention [T1]) and 30 days after the completion of the intervention (follow-up [T2]) (Fig 3).

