#### Physiotherapy

One of the characteristics of the physical therapy program is the practice of functional activities through repeated active, self-generated movements, which will be directly linked to the fulfillment of a goal defined by the child and/or family, such as walking without assistance during recess at school. Thus, the exercises will be individualized and personalized for each child [15].

Physiotherapy will be performed with the aim of minimizing disabilities and accelerating functional independence. According to Luft [16], it is necessary to establish the intensity, motivation and training elements in order for new motor representations and new sensory and motor connections to occur.

Intensity: The participants in both groups will undergo the exercise program for 45 to 60 minutes in two sessions per week for 12 consecutive weeks.Motivation: All exercises will be associated with playful activities, such as ball playing, fishing, etc. The participants may also be take part in a story of princesses and superheroes that enable them to perform the tasks related to the goals [17].Training elements:

The exercises will be performed through the practice of functional training. (Fig 2) Five repetitions of each transition will be performed in each session. The participants will perform strengthening exercise of the lower limb muscles such as knee flexors and extensors and hip adductors and abductors (10 to 20 repetitions). Strengthening the trunk muscles will be performed through functional movements, such as transferring from the lying to sitting position, along with the aid of balls and rolls, including five repetitions in every session. The exercises will be performed with repetitions to promote motor learning as well as improve strength and endurance [4,18,19]. During each session, the participants will be given rest interval between sets.

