#### Criteria for discontinuing intervention

Patients who fail to attend two consecutive sessions or three non-consecutive sessions will discontinue the intervention.

Materials used: Wedges, rolls, medicine balls, steps, balance bean, ankle weights (0.5–1.0 kg), cones, parallel bar, stools of different sizes, mats with different textures, trampoline, walkers.

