#### Calculation of sample size and statistical analysis

The sample size was calculated using the G * Power software (version 3.1.9.2) based on our previous pilot study (F test, repeated-measures ANOVA, intra-between interactions). Considering an effect size of 0.58 for the primary outcome (functional skills) and assuming a possible 10% dropout rate, a total of 30 patients (15 in each group) will be required to reach a 5% significance level with a 90% power. Descriptive statistics will be performed to determine the normality of the data and the mean change (standard deviation, 95% confidence interval) in each group will be calculated. GraphPad PRISM version 7.0 (GraphPad Software—San Diego, CA, USA) will be used for all analyses. A mixed factor ANOVA model will be employed to compare the effects of the interventions in each group in terms of functional variables (PEDI and EMG), quality of life questionnaire and social participation over time (pre-treatment, post-treatment and 30-day follow-up). A 95% confidence interval will be used to establish any differences and a p-value <0.05 will be indicative of a statistically significant difference between groups (two-tailed). If the supposition of normality is not met, pairwise comparisons between groups will be performed using a nonparametric test, as appropriate, for independent samples (Mann-Whitney U test) or dependent samples (Wilcoxon test). The alpha level will be adjusted to 0.0033 (Bonferroni correction) to avoid a type 1 error.

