### Strengths and weaknesses of the study

One of the strengths of this study is its design–a prospectively recorded, randomized, controlled, blind trial. The study will also involve allocation concealment and intention-to-treat analysis. The evaluator responsible for collecting the data will be blinded to the treatment group assignment. The physiotherapists responsible for the treatment have clinical experience and were trained by the main author of the study. Moreover, the study will be guided by the ICF-CY to ensure that the therapists conduct a broad assessment of the children’s activities and participation and determine the focus of the physical therapy intervention. The major limitation of the study is the lack of a control group with healthy children.

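### Intention-to-treat is claimed, but children stopped for poor attendance have no defined T1 or T2, so followed literally the trial would compare attenders

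*Protocol article*

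**What the plan says.** Five places in the protocol article bear on this point.

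- **Strengths and weaknesses of the study:** "The study will also involve allocation concealment and intention-to-treat analysis".
- **Outcome measures:** after the baseline visit T0, the two later visits take place "after 24 sessions of PBM + physical therapy (post-intervention [T1]) and 30 days after the completion of the intervention (follow-up [T2". The text of this section gives no calendar date and no alternative for a child who does not complete.
- **Criteria for discontinuing intervention:** "Patients who fail to attend two consecutive sessions or three non-consecutive sessions will discontinue the intervention".
- **Physiotherapy:** "two sessions per week for 12 consecutive weeks", which is 2 × 12 = 24 slots. Make-up sessions are not mentioned.
- **Calculation of sample size and statistical analysis:** "A mixed factor ANOVA model will be employed to compare the effects of the interventions in each group", over three time points. The total of 30 children is reached "assuming a possible 10% dropout rate".

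**The concern.** Intention-to-treat needs an outcome, or at least an outcome visit, for every randomised child. Here both post-baseline visits hang on an event that the attendance rule prevents for some children.

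Attendance is observed after randomisation and may depend on response, tolerance or family burden. If stopped children have no outcome, the groups compared are no longer the groups randomised. With 15 children per arm, a few unbalanced losses could move the result.

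An analysis plan can choose how to handle missing values. It cannot recover outcomes that the visit schedule never collected, so this has to be settled in the protocol.

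**Working it through.** **1. The passages side by side**

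| Step | Source section | Consequence for a child stopped at, say, session 10 |
|---|---|---|
| T1 follows 24 sessions | Outcome measures | 24 is never reached, so T1 has no date |
| T2 is 30 days after completing the intervention | Outcome measures | no completion, so T2 has no date |
| Absences stop the intervention | Criteria for discontinuing intervention | treatment ends; nothing is said about assessments |
| Three time points, mixed factor ANOVA | Sample size and statistical analysis | only T0 exists; a classical repeated-measures ANOVA drops the child |
| Intention-to-treat | Strengths and weaknesses | cannot be carried out for this child as written |

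The first, second, third and fifth rows rest on the text. The last part of the fourth row is an inference from how the classical method treats an incomplete set of time points.

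**2. The plan's own sample size**

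Inputs from the document: effect size 0.58, within-between interaction, three time points, two groups, alpha 5%, power 90%, dropout 10%, N = 30. Assumed: correlation ρ = 0.5, sphericity, and 0.58 read as d, so f = 0.58/2 = 0.29.

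- Noncentrality λ = f² × N × m/(1 − ρ), with m = 3; df1 = 2; df2 = (N − 2) × 2.
- At N = 27: λ = 0.0841 × 27 × 3/0.5 = 13.62, df = 2 and 50, power 0.904.
- Inflation: 27/0.9 = 30. This reproduces the stated total.

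On this reading the stated power belongs to 27 evaluable children, with room for three losses.

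**3. How often the attendance rule would bite**

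The document gives no absence rate, so q (probability of missing one session) is assumed, with independent absences. The rule is taken as stopping at two absences in a row or at a third absence in total. A child avoids it with no absence, one absence, or two that are not adjacent. Of the 24 × 23/2 = 276 pairs of sessions, 23 are adjacent, leaving 253:

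P(not stopped) = (1 − q)²⁴ + 24q(1 − q)²³ + 253q²(1 − q)²²

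At q = 0.05: 0.292 + 0.369 + 0.205 = 0.865 (unrounded 0.8655), so P(stopped) = 0.135.

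| q | Stopped | Expected of 30 | Chance that more than 3 stop |
|---|---|---|---|
| 2% | 1.8% | 0.5 | 0.2% |
| 3% | 4.5% | 1.3 | 4.3% |
| 5% | 13.5% | 4.0 | 58.8% |
| 10% | 46% | 13.8 | nearly 100% |

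P(stopped) equals 10% at q ≈ 4.3%, which is 24 × 0.043 ≈ 1 missed session per child.

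**4. Power if only complete children are analysed**

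| Evaluable | 0.58 as d (f = 0.29), ρ = 0.5 | 0.58 as f, ρ = 0 | 0.58 as f, ρ = 0.5 |
|---|---|---|---|
| 27 | 0.904 | 0.997 | >0.999 |
| 20 | 0.784 | 0.978 | >0.999 |
| 16 | 0.671 | 0.936 | 0.999 |

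With this noncentrality formula, reading 0.58 as f gives N = 16 (18 with dropout) at ρ = 0 or N = 10 (12 with dropout) at ρ = 0.5, so it does not reproduce 30. A different noncentrality convention, λ = f² × (N − 2) × (m − 1) with f = 0.58, gives 24 (27 with dropout) and power 0.857 at 20 and 0.742 at 16. The power loss therefore depends heavily on a metric and a correlation that the document does not state.

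**The case against.** The strongest reply is that the document never says stopped children go unassessed. The rule ends the intervention; it does not mention follow-up or the analysis set. A mixed ANOVA is compatible with intention-to-treat if those children are still measured or their values are imputed. Rules for missing data may stand in an analysis plan that is not shown, and the SPIRIT figure, also not shown, may hold a schedule. This stands in part. A reader might infer that the protocol prescribes a complete-case analysis or removes stopped children from the study; it says neither. What remains is that the visit definitions in the text give such a child no date.

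A reader might also infer that any child short of 24 sessions loses T1. The documents do not support this. A child with one absence, or two that are not adjacent, continues, and the end of the 24-session programme is a natural reading of T1 for that child. The share with perfect attendance is therefore no measure of exclusion.

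Finally, it is fair to say that the 10% dropout figure cannot be called optimistic on this evidence. At 2% or 3% absence the rule stays well within it, and stopping treatment is not the same as losing data.

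**Conclusion.** The point holds as a conflict between stated passages. The intention-to-treat claim cannot be carried out, as the text stands, for children stopped under the attendance rule, because neither of their outcome visits is defined. If those visits are not held, a classical three-time-point ANOVA would compare attenders.

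The size is illustrative only. Under independent absences, the rule stops from about 1.8% of children at 2% absence per session to 46% at 10%, and passes the dropout allowance at about 4.3%. Complete-case power at 16 evaluable children is 67% if 0.58 is d with correlation 0.5. It is above 93% if 0.58 is f under the same noncentrality formula, and 74% under the other convention. The loss of power is thus uncertain. The undefined visits do not depend on any of these assumptions.

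**What to change.** Leave the attendance rule as it is, and reconcile the sections on physiotherapy, discontinuation, outcome measures, statistical analysis, and strengths and weaknesses:

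1. State that stopping the intervention is not leaving the study.
2. Date T1 by calendar, at the end of the 12-week programme counted from the first session, and T2 30 days later, for every randomised child whatever the number of sessions attended.
3. Analyse all randomised children with a method that keeps partial data. A likelihood-based repeated-measures model is one suitable choice, not the only one.
4. Report sessions attended by arm, and give attenders-only results as supportive.

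The cost is a few sentences, a small number of extra assessments by the existing evaluator, and another statistical package if the named software cannot fit the chosen model. Items 1 and 2 are the essential part and should be in place before any child is stopped.

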**Fig 3 pone.0253963.g003:**
[figure not shown]
SPIRIT statement.

#### Functional skills

The Pediatric Evaluation of Disability Inventory (PEDI) will be used for the assessment of functional independence. The PEDI version validated to Brazilian Portuguese will be used in this study [20]. PEDI is a questionnaire that can be administered in interview form to the parents or caregivers of the children and has three components: I–functional skills (197 items); II–caregiver assistance (20 items); and III–modifications of the environment (20 items). Part I addresses the child’s capacity to perform activities and tasks of daily living. Part II addresses the amount of assistance the caregiver must provide in order for the child to perform activities and tasks of daily living. Part III addresses the number of modifications of the environment used by the child. Each part is subdivided into three domains: self-care, mobility and social function [9]. In the proposed study, only Part I of the mobility domain will be used, which is composed of 65 items. Each item is attributed a score of either 0 (unable to perform) or 1 (able to perform). The total score is obtained by the sum of the items. For the caregiver assistance part, the items will be scored from 0 (completely dependent) to 5 (completely independent) points. The PEDI will be scored according to the instruction manual [21].

#### Quality of life

Quality of life will be assessed using the Child Health Questionnaire—Parent Form 50, which is a useful tool that enables the assessment of a child’s quality of life from the parents’ perspective. This questionnaire has been translated, cross-culturally adapted and validated for the Brazilian Portuguese language [22] and was designed for children five years of age or older, addressing their physical, emotional and social wellbeing from the perspective of parents or caregivers. The questionnaire is composed of 50 items distributed among 15 domains. The final score of each scale ranges from 0 to 100, with higher scores denoting better function or sensation (better quality of life) [23].

#### Participation and environment measure

Changes in participation will be assessed using the Participation and Environment Measure for Children and Youth (PEM-CY), which is a parental report instrument that addresses participation and environmental factors that affect the participation of children in three environments: home (13 items), school (16 items) and community (17 items). For each activity, the parent/caregiver will be asked to provide information on the frequency with which the child participates in one or more activities of this type. The response options are scored on an eight-point scale ranging from never to daily. The parents/caregivers will also be asked to rate the children’s involvement in each activity on a five-point scale from minimally involved to very involved and asked if they wished that their children’s participation changed in this type of activity. The maximum score is 122 points [24]. The PEM-CY version adapted to the Brazilian Portuguese will be used in this study [25].

#### Surface electromyography

Muscle activity will be evaluated using a portable electromyograph (BTS Engineering) synchronized to the BST EMG system. The sit-to-stand activity will be used as the functional measure [26,27]. Electrodes will be placed on the lateral gastrocnemius (LG), tibialis anterior (TA) and rectus femoris (RF) muscles. The preparation of the skin and placement of the electrode will follow the SENIAM recommendations for surface electromyography [28]. The electrodes will be placed with the child in prone position (LG) and supine position (TA and RF). We selected these superficial muscles for surface electromyography as they are deemed primary muscles of the gait cycle [29].

For the evaluation of the sit-to-stand test, the participant will be seated on a chair with hips, knees and ankles flexed at 90° and feet supported on the floor. The child will first be analyzed in the resting position and will then be instructed to stand up, remain in the standing position for 10 seconds and sit down again. The sit-to-stand test will be performed three times with a five-minute interval between tests. The children will perform the movement at the velocity with which they normally do so in their daily routine.

#### Calculation of sample size and statistical analysis

The sample size was calculated using the G * Power software (version 3.1.9.2) based on our previous pilot study (F test, repeated-measures ANOVA, intra-between interactions). Considering an effect size of 0.58 for the primary outcome (functional skills) and assuming a possible 10% dropout rate, a total of 30 patients (15 in each group) will be required to reach a 5% significance level with a 90% power. Descriptive statistics will be performed to determine the normality of the data and the mean change (standard deviation, 95% confidence interval) in each group will be calculated. GraphPad PRISM version 7.0 (GraphPad Software—San Diego, CA, USA) will be used for all analyses. A mixed factor ANOVA model will be employed to compare the effects of the interventions in each group in terms of functional variables (PEDI and EMG), quality of life questionnaire and social participation over time (pre-treatment, post-treatment and 30-day follow-up). A 95% confidence interval will be used to establish any differences and a p-value <0.05 will be indicative of a statistically significant difference between groups (two-tailed). If the supposition of normality is not met, pairwise comparisons between groups will be performed using a nonparametric test, as appropriate, for independent samples (Mann-Whitney U test) or dependent samples (Wilcoxon test). The alpha level will be adjusted to 0.0033 (Bonferroni correction) to avoid a type 1 error.

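### The three-visit ANOVA treats baseline as an outcome level, so the powered test gives no size, direction or timing for the PBM effect

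*Protocol article*

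**What the plan says.** Under Calculation of sample size and statistical analysis, the Protocol article states the model: "A mixed factor ANOVA model will be employed to compare the effects of the interventions in each group". It covers PEDI, EMG, quality of life and "social participation over time (pre-treatment, post-treatment and 30-day follow-up". Baseline is therefore one of the three outcome levels.

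The sample size rests on "F test, repeated-measures ANOVA, intra-between interactions". The inputs are: "Considering an effect size of 0.58 for the primary outcome (functional skills"), "assuming a possible 10% dropout rate", and "a total of 30 patients (15 in each group) will be required to reach a 5% significance level with a 90% power".

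The effect summary is that "the mean change (standard deviation, 95% confidence interval) in each group will be calculated". The section adds that a 95% confidence interval will serve to establish differences, and that a two-tailed p below 0.05 indicates a difference between groups. It names neither the model term nor the contrast. No baseline covariate appears.

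Outcome measures places assessments before therapy, "after 24 sessions of PBM + physical therapy (post-intervention [T1]) and 30 days after the completion of the intervention (follow-up [T2"]). Neither later visit is ranked above the other.

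**The concern.** The aim is to learn what PBM adds to physiotherapy. That calls for an active-minus-sham difference in PEDI mobility, with an interval, at a stated time. The interaction F test says only that the difference between arms is not constant across T0, T1 and T2. Changes within each arm do not answer the question either, because both arms receive physiotherapy and both may improve.

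The T0 score is already collected, but it enters as an outcome rather than as a covariate. With 15 per arm, chance imbalance at baseline is a real possibility, and covariate adjustment deals with it directly. The wording about a difference between groups also leaves room to read the group main effect, which averages in a visit at which no treatment effect can exist.

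**Working it through.** **Inputs.** From the article: 2 groups, visits T0, T1 and T2, N = 30, 10% dropout (30 × 0.9 = 27 completers, 14 v 13), alpha 0.05, power 90%, effect size 0.58 with no metric stated. Assumed, because the article does not give them: correlations between visits, the true effect in SD units, and its time course.

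**1. The plan's own figure.** For the interaction, λ = f²·N·3·ε/(1−ρ), with 2 and 2(N−2) df.
- f = 0.58, ρ = 0.5, ε = 1: N = 10, or 12 after dropout (10/0.9 = 11.1).
- The alternative λ = f²(N−2)·2·ε, with f = 0.58: N = 24, then 27 (28 in equal arms).
- 0.58 read as d, so f = 0.29, ρ = 0.5: N = 28, then 32; 27 completers give 90.4% power.

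The 30 can be neither confirmed nor called wrong. What follows does not depend on it.

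**2. What the 2-df test sees.** Let δ be the between-arm difference at T0, T1, T2. Then f is the root mean square of (δ − mean δ)/2 over the three visits. For δ = (0, 0.8, 0.8) the mean is 0.533, the half-deviations are −0.267, 0.133 and 0.133, and f = √[(0.0711 + 0.0178 + 0.0178)/3] = 0.189. The patterns (0, 0.8, 0), (0, 0, 0.8) and (0, −0.8, −0.8) give the same 0.189.

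**3. Group main effect.** A sustained effect d is averaged as (0 + d + d)/3 = 2d/3.

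**4. Use of baseline at one visit.** In SD² units, a change score has variance 2(1−ρ) and ANCOVA has 1−ρ². The ratio is (1+ρ)/2: 0.75, 0.85, 0.90 and 0.95 at ρ = 0.5, 0.7, 0.8 and 0.9. For an assumed 0.8 SD difference at 90% power, n per arm for change v ANCOVA is 33 v 25, 20 v 17, 14 v 12 and 7 v 7.

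**5. Simulated power (%).** The three figures in each cell are for ρ = 0.5/0.7/0.8 in blocks A and B. In block C they are for correlations (T0T1, T0T2, T1T2) of (0.6, 0.55, 0.9), (0.7, 0.65, 0.9) and (0.8, 0.75, 0.95). In block A the effect is set so that the interaction has 90% when the effect is sustained: about 1.22 SD at ρ = 0.5, 1.22 × √(0.3/0.5) = 0.95 at 0.7, and 0.77 at 0.8.

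| Scenario | Interaction, uncorrected | ANCOVA at T1 | ANCOVA on mean of T1 and T2 |
|---|---|---|---|
| A. Equal correlations, 14 v 13: sustained | 90/90/90 | 93/90/88 | 99/97/96 |
| A. Halves by T2 | 79/79/79 | 93/90/88 | not run |
| A. Half at T1, full at T2 | 79/79/78 | 40/37/35 | not run |
| A. At T2 only | about 90 | about 5 | not run |
| B. Equal correlations, 0.8 SD, 13 per arm: sustained | 52/75/91 | 60/77/89 | 77/89/96 |
| B. Halves by T2 | 41/62/81 | 60/76/89 | 53/67/80 |
| B. Gone by T2 | 52/76/91 | 60/76/89 | 27/36/47 |
| C. Unequal correlations, 0.8 SD sustained, 14 v 13 | 67/77/90 | 69/78/90 | 69/79/89 |

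In the first row of A, the group main effect has 70/42/28%. In C, the interaction with a Greenhouse-Geisser correction has 60/72/86%.

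**6. Type I error.** Under the null with the block C correlations, the uncorrected interaction rejects in about 6.4 to 7.1% of trials at nominal 5%. Greenhouse-Geisser gives 4.7 to 5.2%, and ANCOVA at T1 about 5%.

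**The case against.** A mixed ANOVA is a valid analysis, and its indifference to timing is a legitimate reason to choose it. The article does not say when the PBM effect should peak. If the effect builds after T1, the interaction keeps 79% power while ANCOVA at T1 falls to 35 to 40%. That stands, and it rules out presenting a T1-only contrast as a safe improvement.

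It can also be said that the section mentions a confidence interval for differences, and that 0.0033 = 0.05/15 matches the 15 pairs among six group-by-visit cells, so pairwise follow-up may be intended. It may be. But 15 is also the number of domains that the article gives for the quality-of-life questionnaire, and no comparison is singled out as the PBM effect.

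A reader might infer several stronger things that the article does not support:
- **That the baseline score is wasted.** It is used, by differencing; the loss is one of efficiency.
- **That the F test runs above its nominal level.** This holds only without a sphericity correction and under unequal correlations. T0 to T1 spans 12 weeks and T1 to T2 only 30 days, so unequal correlations are plausible. But the article does not say that the test is uncorrected, and a correction restores about 5%.
- **That a significant interaction might not reflect treatment at all.** Under randomisation, a true interaction requires an effect at T1 or T2. Only its direction and timing are unresolved, and the cell means would show them descriptively.
- **That the group main effect is the planned test.** The only term named is the interaction, in the sample-size statement; the decision rule leaves the term open.

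**Conclusion.** The point holds as one of estimand and clarity, with a modest and uncertain efficiency gain. The article fixes an omnibus 2-df test on three visits that include baseline, describes only within-arm changes, and singles out no active-minus-sham PEDI contrast. This is a stated choice of method, so it is not merely detail left to an analysis plan.

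Against the uncorrected interaction, the power gain is at most about 3 points, and can be nil, when T1 and T2 are highly correlated. Under equal correlations and a sustained effect, the mean of T1 and T2 gains up to about 9 points when the interaction starts at 90%. The gain is larger when it starts lower: 25 points at ρ = 0.5 and 0.8 SD. It can reverse: if the effect is gone by T2, the mean contrast has 27% against 52% at ρ = 0.5. All these figures rest on assumed correlations, effect sizes and time courses. The case for change therefore rests mainly on obtaining a directed, interpretable effect. The change is worth making, but the planned test is not invalid.

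**What to change.** Analyse PEDI mobility at T1 and T2 in a repeated-measures model adjusted for T0 with unstructured covariance, or by ANCOVA. Report the active-minus-sham difference with its 95% CI and p-value.

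State in advance which contrast is primary. T1 fits if the question is the effect at the end of treatment. The mean of T1 and T2 fits if the timing is uncertain: under equal correlations it roughly matches or exceeds the interaction when the effect at one visit is half that at the other, but it does worse if the effect exists at one visit only. The article does not settle this, so the sponsor must. Report the other contrasts as secondary, and treat the remaining continuous outcomes in the same way.

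If the interaction is kept as a supporting test, state the sphericity correction. Restate the sample-size basis for the chosen contrast, giving the metric of 0.58 and the assumed correlation.

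The cost is analysis wording only: no new data, visits or patients. The article names GraphPad Prism 7.0 for all analyses, so the sponsor should confirm that it fits the chosen model or name another package. The real downside is the loss of power if the primary contrast is placed at the wrong time.

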The therapeutic effect of phototherapy is achieved through the application of monochromatic or narrow-band light in tissues. PBM influences cell activity through the stimulation or inhibition of chemical and physiological functions [5]. The magnitude of the effect of PBM is influenced by the wavelength, energy density (fluence), power density, type of injury and absorption spectrum of the photoreceptor. Photons stimulate chemical changes in the interior of the cell, causing biological reactions, triggering neuroprotective responses, improving metabolism and blood flow as well as diminishing inflammatory processes and oxidative stress. As a result of these benefits, PBM has been widely used as an adjuvant in the treatment of numerous diseases [5,10,11].

Studies involving an experimental model of spinal cord injury have demonstrated that both the red and infrared wavelengths have the potential to be an effective, non-invasive means of therapy, promoting axonal sprouting, an increased concentration of glial cells and nerve connections as well as improvements in function and sensitivity [12,13]. In a clinical trial involving individuals with spinal cord injuries, PBM exerted positive effects on motor function, especially during isotonic contraction of the stimulated muscles, which were assessed using electromyography (EMG) [14]. Thus, the combination of physical therapy and PBM is promising treatment for individuals with MMC.

Therefore, the aim of the proposed study is to evaluate the effects of photobiomodulation combined with physical therapy on the functional performance of children with low lumbosacral myelomeningocele. We hypothesise that a photobiomodulation combined with physical therapy may enhance functional performance and health-related quality of life of children with MMC.

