## Discussion

This randomized clinical study will expand our understanding of how physical therapy combined with photobiomodulation can affect functional performance, participation and quality of life in children with low lumbosacral myelomeningocele. Thus, the study will assist in optimizing future rehabilitation interventions for this population. Moreover, few studies have evaluated the effects of rehabilitation in children with myelomeningocele.

The proposed protocol is expected to improve functional performance, participation and quality of life in these children. In the rehabilitation process for children with MMC with the aim of achieving independence on activities of daily living, it is necessary for healthcare providers to have a holistic view of the child and his/her disability [20]. Individuals with MMC are known to have difficulties in functional participation, mainly concerning self-care, housing, and functional mobility, leading to diminished quality of life [30]. Physical therapists have used several outcome measures to evaluate gross motor function in children with MMC, such as the PEDI questionnaires, based on observing the children’s abilities [26]. The sit-to-stand task is an accessible tool applied to evaluate the functional strength of the lower limbs. The ability to rise from a seated position is one of the most fundamental movements among normal daily living activities, such as walking or going to the bathroom [31]. Among children with MMC, the sit-to-stand task is a reliable outcome measure, which has been examined regarding reliability and concurrent validity in children with MMC [32]. On the other hand, sit-to-stand activity is a complex activity that should be investigated in terms of its electromyographic features [33].

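### The statistical section sets two significance levels, 0.05 and 0.0033, without saying which tests each governs, so error control over the quality-of-life, participation and EMG scores is undefined

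*Protocol article*

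**What the plan says.** All the decision rules stand in one paragraph of the protocol article, under Calculation of sample size and statistical analysis.

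- **Primary outcome.** The sample size rests on one outcome: "Considering an effect size of 0.58 for the primary outcome (functional skills) and assuming a possible 10% dropout rate". It is set for a 5% significance level and 90% power, using the group-by-time interaction of a repeated-measures ANOVA.
- **Model.** One mixed ANOVA over three visits is applied to PEDI, EMG, the quality-of-life questionnaire and social participation.
- **First threshold.** Straight after the model comes: "a p-value <0.05 will be indicative of a statistically significant difference between groups (two-tailed").
- **Fallback.** Next: "If the supposition of normality is not met, pairwise comparisons between groups will be performed using a nonparametric test", either Mann-Whitney or Wilcoxon.
- **Second threshold.** The paragraph closes: "The alpha level will be adjusted to 0.0033 (Bonferroni correction) to avoid a type 1 error". It gives no number of tests and no family.

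The outcome sections show that the other measures yield several scores. For the CHQ-PF50, "The questionnaire is composed of 50 items distributed among 15 domains", each scale runs from 0 to 100, and no summary score is named. The PEM-CY covers "home (13 items), school (16 items) and community (17 items"), although one maximum of 122 points is also given. EMG is recorded on three muscles.

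The Introduction hypothesises that the combined treatment "may enhance functional performance and health-related quality of life of children with MMC". The Discussion adds: "The proposed protocol is expected to improve functional performance, participation and quality of life in these children".

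**The concern.** A p-value between 0.0033 and 0.05 on a CHQ domain, a PEM-CY score or an EMG variable counts as significant under one sentence and not under another in the same paragraph. The choice could then be made after the results are seen.

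This matters most for quality of life and participation. Quality of life is half of the stated hypothesis and participation is a stated expected benefit, so a favourable result is likely to be reported as a finding. If each score is tested at 0.05, one chance result among many could be presented as support. If 0.0033 applies to all of them, that risk is largely removed. The plan does not say which situation holds.

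**Working it through.** **1. Reproduce the plan's figure.** 0.05/15 = 0.00333, which rounds to the stated 0.0033. Two families of 15 can be found in the document:
- the 15 CHQ-PF50 domains (Quality of life section);
- all pairs among 2 arms × 3 visits = 6 cells, C(6,2) = 6 × 5/2 = 15.

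The first would correct across quality-of-life scores. The second would correct within one outcome and give no protection across outcomes.

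**2. Count the secondary scores (inferred).** 15 CHQ domains + 3 PEM-CY settings + 3 muscles = 21. With one PEM-CY total, 15 + 1 + 3 = 19. The document names no EMG variable, so one per muscle is an assumption. Separate PEM-CY frequency and involvement scores would raise the count.

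**3. Family-wise error under each reading.** Assume PBM has no effect. For k independent tests at level α, the chance of at least one false positive is 1 − (1 − α)^k:
- 21 tests at 0.05: 1 − 0.95^21 = 0.66. 19 tests: 1 − 0.95^19 = 0.62.
- 15 CHQ domains at 0.05: 1 − 0.95^15 = 0.54.
- 15 at 0.0033 plus 4 or 6 at 0.05: 1 − 0.9967^15 × 0.95^4 = 0.22, and 1 − 0.9967^15 × 0.95^6 = 0.30.
- 21 tests at 0.0033: 1 − 0.9967^21 = 0.067 (Bonferroni bound 21 × 0.0033 = 0.069).

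The scores will be correlated, but the document gives no correlation. The table uses simulated equicorrelated two-sided normal tests (400,000 draws), with the correlation assumed.

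| Reading | Correlation 0 | 0.5 | 0.8 |
|---|---|---|---|
| 15 CHQ domains at 0.05 | 0.54 | 0.36 | 0.20 |
| 19 scores at 0.05 | 0.62 | 0.41 | 0.22 |
| 21 scores at 0.05 | 0.66 | 0.43 | 0.23 |
| CHQ at 0.0033, other 4 to 6 at 0.05 | 0.22–0.30 | 0.17–0.22 | 0.12–0.14 |
| 21 scores at 0.0033 | 0.07 | 0.05 | 0.02 |

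A separate simulation of the ANOVA itself (8,000 null trials, 15 children per arm, three visits, within-child correlation 0.6, interaction F on 2 and 56 df) agrees at correlation 0.5: 0.38 for 15 scores and 0.45 for 21 at 0.05; 0.23 for 15 at 0.0033 plus 6 at 0.05; 0.048 for all 21 at 0.0033.

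**4. False results that favour PBM.** Take only the 18 quality-of-life and participation scores (15 + 3). Treat each as one two-sided contrast at 0.05, so that 0.025 lies in the favourable direction. If independent: 1 − 0.975^18 = 0.37. Simulated: 0.20 at correlation 0.5 and 0.11 at 0.8. At 0.0033 for every score, the independent figure is about 0.029.

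**5. Which reading the text favours.** The 0.05 sentence directly follows the ANOVA sentence, and the sample size for the interaction test uses 5%. The 0.0033 sentence follows the nonparametric pairwise fallback. This points to 0.05 for the ANOVA tests, but no sentence limits 0.0033 to the fallback.

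**The case against.** A reader might infer that every secondary score is simply tested at 0.05, on at least 21 scores, so that a false claim for PBM on quality of life or participation is likely. The document does not support that.

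- **The Bonferroni sentence is there and is unrestricted.** If it covers the CHQ domains, the error for quality of life is at most 15 × 0.0033 = 0.0495. If it covers all scores, the rate is about 0.05. The large figures arise only if 0.05 governs the ANOVA tests.
- **21 is not a lower bound.** A single PEM-CY total is possible, which gives 19, and the EMG variables are not specified.
- **Likely is too strong.** Even at 0.05 throughout, the chance of a false favourable quality-of-life or participation result is about 0.20 at correlation 0.5, and 0.37 if the 18 scores are independent. The figures of 0.41 to 0.43 also include EMG and results against PBM.

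It can also be said that a condensed article may leave a lead secondary score, a testing order or an exploratory label to an analysis plan not shown here, and that the Introduction and Discussion express hopes rather than declare confirmatory tests.

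All of this limits the size and certainty of the point. It does not remove it: two thresholds that give opposite conclusions on the same p-value are stated in this text, so the decision rule is fixed badly and is not merely left for later.

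**Conclusion.** The point holds as an unresolved decision rule. The document supports the finding that 0.05 and 0.0033 are both stated without their scope. It does not establish that the secondary outcomes are uncorrected.

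The consequence depends on the reading, over an inferred 19 to 21 secondary scores:
- 0.05 for all ANOVA tests: family-wise error about 0.41 to 0.43 at correlation 0.5 (about 0.22 to 0.66 for correlations from 0.8 to 0).
- 0.0033 for the CHQ domains only: about 0.17 to 0.22 at correlation 0.5.
- 0.0033 for every secondary score: about 0.05, at most 0.07.

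The first reading fits the order of the sentences and the sample-size level best, but the text does not settle it. The correlations and the score count are assumptions. The authors should correct this; it does not invalidate the design.

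**What to change.** Reword the end of the statistical section:

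1. State that the group-by-time test on the PEDI functional-skills mobility score is the only confirmatory test, at two-sided 0.05.
2. State the family that 0.0033 covers and what its 15 tests are, or remove the sentence.
3. Then choose one of two rules for the rest:
   - label CHQ-PF50, PEM-CY and EMG exploratory, report estimates with 95% confidence intervals, and make no efficacy claim from a single p<0.05; or
   - test quality of life only after PEDI is significant, using Holm at a total of 5% over the 15 CHQ domains or one CHQ score named before unblinding, with PEM-CY and EMG exploratory.
4. Bring the quality-of-life and participation statements in the Introduction and Discussion into line with that choice.

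This needs no new data and no extra patients. The cost is that an isolated secondary p<0.05 can no longer be presented as proof of benefit.
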